### 7.2 Visits

#### Screening visit

1. Information of participants and their parent(s) and confirmation of consent
2. Assessment of inclusion and exclusion criteria
  - Medical and psychosocial history
  - K-SADS-PL
  - IQ test
  - Social Communication Questionnaire (SCQ)
  - Assessment of MRI criteria
  - Pregnancy test (urine test)
3. Assessment of participants' characteristics
  - Edinburgh Handedness Inventory (child)
  - Social economic status of the parent(s)
  - Pubertal Developmental Scale (child, parent)
  - Expectations and concerns towards tDCS (child/parent)
  - ADHD rating scale (parent)\*
  - Quality of Life (KIDSCREEN-27, child/parent)\*

*The last two questionnaires\* can be filled out at home and be returned at baseline.*

**Baseline visit (Visit 0, within 4 weeks after screening)**

- Assessment of arousal, mood and motivation before and after the session (SAM, VAS, diary)
- Resting state, 64-channel EEG
- Neuropsychological performance (tasks: n-back, Flanker, CPT), 64-channel EEG
- Assessment of adverse events
- Randomization

**Baseline visit (Visit 0\_MRI, within 4 weeks after screening), if participants are eligible for MRI**

- Assessment of arousal, mood and motivation before and after the session (SAM, VAS, diary)
- Structural MRI (T1-weighted, T2-weighted)
- Resting state fMRI
- Diffusion tensor imaging (DTI)

**Visit 1 to 10 (V1 within 4 weeks after V0)**

- Assessment of arousal, mood and motivation before and after the session (SAM, VAS, diary)
- Multichannel stimulation (sham/real) of either the dlPFC (**Study A**) or the rIFG (**Study B**) during a task
- EEG before and after the multichannel stimulation
- Assessment of adverse events during stimulation (safety questionnaire)
- Assessment of adverse events

**Visit 11 (Post assessment within 7 days after V10)**

- Assessment of arousal, mood and motivation before and after the session (SAM, VAS, diary)
- Resting state, 64-channel EEG
- Neuropsychological performance (tasks: n-back, Flanker, CPT), 64-channel EEG
- ADHD rating scale (parent)
- Assessment of adverse events

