**Visit 12 (Follow-up, 4 to 5 weeks after Visit 10)**

- Assessment of arousal, mood and motivation before and after the session (SAM, VAS, diary)
- Resting state, 64-channel EEG
- Neuropsychological performance (tasks: n-back, Flanker, CPT), 64-channel EEG
- ADHD rating scale (parent)
- Quality of Life (KIDSCREEN-27, child/parent)
- Expectations and concerns towards tDCS (child/parent)
- Assessment of adverse events

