#### ***Decision of investigator or Sponsor***

Moreover, the investigator can decide to end study participation if there is reason to assume that the intervention is harmful for the child/adolescent or that study participation is mainly motivated by the parent and is not wished for by the child/adolescent. Reasons for exclusion from the study will be documented in the electronic Case Report Form (eCRF).

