## 11.1 Sample size calculation

The sample size for **Study A** and **Study B** is calculated separately for each study using a two-sided t-test (significance level  $\alpha=0.05$ ) with a power  $1-\beta=80\%$  based on a medium expected effect size of  $d=0.6$ . Previous studies in ADHD have shown similar or larger effect sizes for tDCS. This result leads

to a required sample size of 45 patients per group (G\*Power3.1); assuming 10% drop-out, the total sample size consists of 200 randomized patients (100 patients for each study). In **Study A**, 50 patients will be allocated randomly to Arm A, whereas the remaining 50 patients will be randomized to Arm B. The same procedure will be repeated for **Study B**.

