### 11.3.2 Analysis population

The primary analysis will be based on the intention-to-treat (ITT) set, including all randomized patients irrespective of the amount of treatment actually received. A per-protocol (PP) analysis will be performed as sensitivity analysis. All participants will be asked to participate in the end-of-treatment and follow-up assessment, even if they drop out of treatment, to minimize the number of those who are lost to follow-up. Deviations from the protocol that lead to exclusion from the PP-set will be detailed in the SAP.

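### V11 and V12 have no date for a child who stops stimulation before V10, and two exclusion rules conflict with seeking the primary outcome from every randomised child

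*Combined protocol and SAP*

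**What the plan says.** **Timing.** Protocol 7.2 sets V11 as "Post assessment within 7 days after V10" and V12 as "Follow-up, 4 to 5 weeks after Visit 10". The synopsis agrees on both. The examination plan also counts V11 from V10, but gives V12 as within four weeks of V11. The SAP's only timing rules are in its protocol-violation list (5.2). They too count from V10: more than 8 days to V11, or less than 4 weeks to V12, is a violation.

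**Who should be assessed.** Protocol 11.3.2 and the synopsis define the primary set as all randomised patients, and ask all of them to attend the post and follow-up assessments "even if they drop out of treatment, to minimize the number of those who are lost to follow-up". Section 7.4.2.1 says consent to primary-outcome assessment will be sought from all randomised patients, above all those who discontinue treatment.

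**Who may leave.** Under the investigator or sponsor decision in 7.4.2.1, "the investigator can decide to end study participation if there is reason to assume that the intervention is harmful for the child/adolescent". That paragraph does not mention outcome assessment. The compliance paragraph ends further treatment only, and adds outcome assessment where possible. Section 7.1.3 excludes any participant who is unblinded, without saying from what. Section 8.8 calls for unblinding when a serious event is suspected to be device-related.

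**Missing values.** SAP 7.6 uses multiple imputation under MAR for the primary analysis. Its sensitivity analyses are a repeated-measures mixed model using V11 and V12, a complete case analysis, and worst-best case scenarios under MNAR.

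**The concern.** The plan asks for a measurement from early stoppers without saying when to take it. Sites must choose, and time since the last stimulation then differs between children for reasons unrelated to the arm comparison.

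The routes out of treatment also lead to different data. Family withdrawal and non-compliance keep the outcome in view. Suspected harm and unblinding can be read as ending it. Children on the safety routes are the ones whose missing values are least safely treated as missing at random. If they lack V11, the primary analysis fills them in under MAR, and the all-randomised estimate can move towards the effect in children who completed. This matters here because both documents put the emphasis on effect-size estimates and confidence intervals.

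**Working it through.** **1. The plan's own figures.** Protocol 11.1 uses a two-sided t-test for each study, alpha 0.05, power 80%, d = 0.6, and arrives "to a required sample size of 45 patients per group (G\*Power3.1); assuming 10% drop-out". The exact noncentral-t calculation gives 44.59, so 45 per group. Then 45/0.90 = 50 per arm, 100 per study and 200 in total. The figures reproduce. Power is 80.4% with 45 per arm and 84.4% with 50. The allowance already treats 5 children per arm as giving no outcome, so the point concerns bias and comparability, not sample size.

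**2. The timing rules side by side.**

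| Place | V11 | V12 |
|---|---|---|
| Synopsis; protocol 7.2 | up to 7 days after V10 | 4 to 5 weeks after V10 |
| Examination plan | up to 7 days after V10 | up to 4 weeks after V11 |
| SAP 5.2 | violation if over 8 days after V10 | violation if under 4 weeks after V10 |

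Every V11 rule needs a V10. V12 needs either V10 or a V11 that itself needs V10. Neither is dated without V10.

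**3. How far site choices can differ.** Call V1 day 1. On the planned schedule (five days, two off, five days) V10 is day 12 and a completer's V11 falls on days 13 to 19. If sessions are delayed to the three-week limit, V10 is at latest day 22 and V11 day 29. Take a child who stops after session 3, on day 3:
- 7 days counted from the last session: V11 on days 4 to 10.
- 7 days counted from the planned V10: V11 on days 13 to 19.
- 7 days counted from the latest allowed V10: V11 up to day 29.

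The first two windows do not overlap, and the documents do not choose between them.

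**4. The exit routes side by side.**

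| Route | What ends | Outcome assessment |
|---|---|---|
| Family decision (7.4.2.1) | participation, at their choice | consent sought |
| Non-compliance (7.4.2.1) | further treatment | where possible |
| Suspected harm (7.4.2.1) | study participation, at the investigator's discretion | not mentioned in that paragraph |
| Unblinding (7.1.3) | participant excluded | not mentioned |

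The last two rows need reconciling with 11.3.2 and with the all-randomised sentence in 7.4.2.1.

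**5. Illustration of size.** The share *q* of the active arm that stops early and the fraction *r* of effect they retain are not in the documents, so both are assumptions. Suppose completers have d = 0.60, no stopper has V11, and imputation reproduces the completer effect.
- All-randomised effect = 0.60 × [1 − q(1 − r)].
- q = 0.10, r = 0.5: 0.60 × 0.95 = 0.57. Overstatement 0.60/0.57 = 1.05.
- q = 0.10, r = 0: 0.60 × 0.90 = 0.54. Overstatement 0.60/0.54 = 1.11.
- q = 0.05, r = 0: 0.60 × 0.95 = 0.57. Overstatement 1.05.
- Unadjusted standard error of d at 50 per arm: about √(2/50) = 0.20. The gaps of 0.03 and 0.06 are 0.15 and 0.30 standard errors.
- If half the stoppers are assessed (q = 0.10, r = 0), 47.5 of 50 in the active arm are observed, with mean effect 45 × 0.60/47.5 = 0.57, against 0.54. The overstatement is again about 5%.

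**The case against.** The plan does provide for assessing early stoppers. The synopsis, 7.4.2.1 and 11.3.2 all ask for it, and the sentence in 7.4.2.1 covers all randomised patients, not only those whose family withdraws. **This stands:** what is missing is the timing, not the intention to collect. A reader might infer that suspected harm automatically removes a child from assessment. The documents do not say so, because the investigator's power is discretionary and can be read together with the all-randomised sentence. The conflict is that the text also allows the opposite reading, and the unblinding rule is not discretionary.

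A reader might also equate the 10% drop-out with children who never reach V10. **The documents do not support that.** It is a sample-size allowance; some drop-outs may leave after V10, and some early stoppers may be measured.

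The SAP's MNAR scenarios address informative missingness directly. They bound the result, which softens the concern, but they do not recover the data or standardise the timing of values that were observed. The mixed model borrows from V12, which is equally undated.

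The imputation model is not specified, so it is an assumption that imputed values resemble completers. Task performance is recorded at each session and could inform the imputation. Finally, protocol 1.2.2 reports that no participant dropped out because of adverse events in the consortium's earlier studies, so the safety route may hold few children. These points limit the likely size; they do not close the gap.

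**Conclusion.** The point holds in a limited form. No V11 or V12 timing exists for a child who stops before V10, the two V12 anchors disagree, and 7.1.3 and the investigator-decision paragraph of 7.4.2.1 conflict with the provisions that seek the outcome from every randomised child.

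The plausible effect is modest: about 5% to 11% of the estimate, or 0.15 to 0.3 standard errors, if 10% of the active arm stop early and none is measured. The upper figure is a corner case that also needs zero retained benefit and imputation that mirrors completers. It is not a forecast, and it describes missing outcomes; a child measured at an irregular time is not imputed, and the harm there is loss of comparability.

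A reader might conclude that the intention-to-treat analysis cannot be done. It can, through imputation and the planned sensitivity analyses. The weakness is that it may rest on imputed or inconsistently timed values for the most informative children. This should be corrected, but it does not undermine the design.

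**What to change.** **Protocol 7.2 and examination plan.** State that, for a child who stops stimulation before V10, V11 is held within 7 days after the date on which V10 was scheduled, and V12 is counted from that same date. Reconcile the two V12 anchors. Record the scheduled V10 date and the date of the last session in the eCRF.

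**Protocol 7.1.3 and 7.4.2.1.** Reconcile these with 11.3.2 so that ending stimulation, or unblinding, does not by itself end outcome and adverse-event assessment or remove the child from the ITT set, unless consent or assent to assessment is withdrawn. That condition protects a child who does not wish to continue. When and why stimulation is stopped stays as it is.

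**SAP 7.3 and 7.6.** State that V11 values observed after early stopping are used in the ITT analysis. This does not belong in 5.2, which lists per-protocol exclusions.

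**Cost.** A few sentences in each document and two date fields. No visits are added, since V11 and V12 are already planned for every child, and the sample size is unchanged. If follow-up has already closed, the SAP part can still be done, with a table of early stoppers by arm, reason and actual V11 timing.

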**Visit 11\_MR (MRI, within 7 days after V10), if participants are eligible for MRI**

- Assessment of arousal, mood and motivation before and after the session (SAM, VAS, diary)
- Resting state fMRI
- Assessment of adverse events

**Visit 12 (Follow-up, 4 to 5 weeks after Visit 10)**

- Assessment of arousal, mood and motivation before and after the session (SAM, VAS, diary)
- Resting state, 64-channel EEG
- Neuropsychological performance (tasks: n-back, Flanker, CPT), 64-channel EEG
- ADHD rating scale (parent)
- Quality of Life (KIDSCREEN-27, child/parent)
- Expectations and concerns towards tDCS (child/parent)
- Assessment of adverse events

### 7.3 Study related procedures

#### (I) Pregnancy test

Female participants who already experienced their menarche are required to provide a urine sample during screening. Pregnancy will be determined via standard laboratory procedure at the site.

#### (II) Verbal assessments

##### *Medical and psychosocial history*

Covers developmental milestones, past and present somatic illnesses and treatment (surgery), past and current medication, ADHD treatment history

##### *K-SADS-PL*

To inquire about ADHD symptoms and relevant comorbidities, all sites will use the Revised Schedule for Affective Disorders and Schizophrenia for School-Age Children: Present and Lifetime Version (K-SADS-PL) (Kaufmann et al., 1997; Delmo et al., 2000) which generates diagnoses by integrating the child's and parents' reports. This semi-structured interview is especially suited due to its high inter-rater reliability as well as concurrent validity with clinical rating scales (Kaufmann et al., 1997; Kim et al., 2004). Moreover, it is very frequently used and well accepted in international research on ADHD.

#### (III) Written assessments / questionnaires (all are available in Portuguese and German)

##### *Socioeconomic status of the parent(s)*

Socioeconomic status will be determined for the parent the child lives with most of the time. It is derived from the net income of the household, school graduation level and the current professional situation of the parent according to Lampert et al. (2014). This approach has been employed in a large German health survey in children and adolescents (Lampert et al., 2014). It allows a differentiation in low, middle, and high socioeconomic status.

##### *Social Communication Questionnaire*

We will use the well established Social Communication Questionnaire (SCQ) as an additional diagnostic tool (Rutter et al., 2003). It consists of four scales: social interaction, communication, abnormal language, and stereotyped behavior and has satisfactory internal consistency coefficients (.84 to .93) across age groups. The SCQ provides a cut-off score indicating the likelihood of autism spectrum disorder in an individual. The SCQ consists of 40 questions and can be applied in less than 10 minutes.

##### *Intelligence*

To screen for general intelligence, the German sites will use the first part of the Culture Fair Intelligence Test – Scale 20 (CFT-20-R) (Weiss, 2008) which is a basic non-verbal measurement of general cognitive abilities particularly of cognitive flexibility and problem solving (*duration: 20 min.*, retest reliability: .72 to .91, average correlation with other intelligence assessments e.g. Wechsler Scales: .64). Coimbra will use the performance IQ of the WISC-III which also focusses on non-verbal intellectual skills (*duration: 30 min.*, retest reliability: .74 to .77). In case IQ assessments using the CFT-20 R (Germany) or the WISC-III (Portugal) are obtainable that are not older than a year, IQ tests do not need to be redone.

##### *Edinburgh Handedness Inventory (EHI)*

To control for participants' handedness we will use the Edinburgh Handedness Inventory (Oldfield, 1971). The EHI is a short, 10-item scale used to assess the dominance of a person's right or left hand in everyday activities and is widely used in research studies (*duration: 5 min.*).

##### *Pubertal Development Scale (PDS)*

Using only three items of the *Pubertal Development Scale* (PDS, (Watzlawik, 2009) allows to measure the pubertal stage without visual inspection by a clinician. The single sum score differentiates five different pubertal stages for boys and girls (*duration: 3 min.*; Cronbach's alpha: .59 to .71 self-ratings, .64 to .81 parental ratings.).

##### *ADHD rating scale*

The ADHD rating scale comprises all 18 diagnostic criteria (9 inattentive / 9 hyperactive/impulsive) for ADHD according to the DSM-V. Parents and participants rate the frequency of each symptom on a four-step scale. The rating scale allows for separate calculation of overall symptom load, as well as for severity of inattentive and hyperactive/impulsive symptoms (*duration: 10 min.*).

**KIDSCREEN-27**

The KIDSCREEN-27 allows to assess health-related quality of life in children and adolescents (age: 8 to 18) and has been widely used in international European health surveys (Ravens-Sieberer et al., 2005; Ravens-Sieberer and Europe, 2006). It measures quality of life in different domains, namely *Physical Well-Being*, *Psychological Well-Being*, *Autonomy & Parents*, *Peers & Social Support* and *School Environment* (duration: 10-15 min., reliability of each domain > .7).

**Expectations and concerns of parents and participants towards tDCS**

In order to investigate motivation/intention towards application of tDCS in pediatric population, a special questionnaire was developed based on the well-established theory of planned behavior (TPB) (Ajzen, 1991). The TPB aims to predict and understand why an individual may perform certain behaviors. Behavioral intention is a product of distal constructs such as attitude, normative beliefs, and perceived behavioral control. Research supports the usefulness of the TPB in the prediction of behavioral intention and performance for a wide variety of health behaviors and behavioral interventions (McEachan et al., 2011). The TPB enables not only an assessment of the strength of motivation/behavioral intention (for example towards application of tDCS) but also a differentiation which of the mentioned constructs is essential for explaining attitudinal changes and needs to be considered to improve adherence to a specific intervention (McDermott et al., 2016) (duration: 5 minutes). In addition, four open questions regarding expectations and concerns towards tDCS will be posed to children and parents in the course of the clinical interview.

**Safety questionnaire**

All sites will use the questionnaire of sensations related to transcranial electrical stimulation (TES) to assess discomfort during the stimulation (Poreisz et al., 2007). Participants are asked to rate a variety of sensations e.g. itching, burning on a four-step scale (duration: 5 min).

**Self Assessment Manikin (SAM)**

The Self-Assessment Manikin (SAM) scales are a well-established, non-verbal (pictorial) rating system to obtain self-assessments of experienced emotions on the dimensions affective valence, dominance and arousal in adults and children (Bradley and Lang, 1994). All sites will use this method (three 9-point scales) to measure the emotional state/mood (duration: 1 min; Cronbach's alpha: .63 to .98).

**Visual analogue scale (VAS) for motivation and alertness**

On two 10-cm VASs we will assess the current motivation (0 = not at all; 10 = highly motivated" and alertness (0 = very tired; 10 = very alert) in the beginning and in the end of all visits (duration: 1 min).

**Diary**

Participants are asked for acute consumption of caffeine, energy drinks or intake of medication, occurrence of significant events in school or at home in the beginning of visits 0-12 (duration: 3 min).

**(IV) Neurobiological assessments/measures**

**MRI measures** (structural T1 and T2, resting state fMRI, DTI) are collected at all sites using 3T scanners (Coimbra: Siemens TRIO; Frankfurt: Siemens TRIO, Kiel: Philips Achieva; Magdeburg: Siemens PRISMA), which have been employed at all sites for the investigation of children and adolescents. Acquisition settings were developed and defined to provide sufficient data amount and quality to develop biologically-driven models for the prediction of inter-individual variability in response to tDCS as well as to apply individual head modeling and electrical current estimation. The MRI session (V0\_MRI) will last approximately *one hour*, V11\_MRI about 30 minutes.

**EEG** during baseline, post-intervention and follow-up will be collected from 64-channels to identify electrophysiological changes due to the intervention. A larger array of electrodes is used to be able to investigate connectivity features (duration: *about 2 hours*)

SOPs are specified for all measures to ensure homogeneity of data quality at all sites.

### (V) Intervention: tDCS

- All sites will use an optimized multi-channel montage to target the dlPFC (**Study A**) or the rIFG (**Study B**) (see Figure 3)

[figure not shown]

Figure 3: Optimized multi-channel montage for (upper row) dlPFC (Study A) and (lower row) rIFG (Study B). Red circles indicate locations of anodal electrodes, blue circles indicate locations of return electrodes.

- EEG will be recorded prior and post to real/sham stimulation in all patients to control for stimulation effects on brain activation. EEG during stimulation can require time-intensive readjustment of electrodes before starting stimulation. Concurrent EEG will therefore only be recorded in patients where no substantial readjustment is necessary to keep strain during the intervention at a minimum.
- Real stimulation: 1 mA, stimulation duration 20 min.
- Control intervention: sham stimulation (30 s ramp up – 30 s ramp down)
- Participants will take part in 10 sessions within a time interval of three weeks. We will aim to schedule 2 x 5 consecutive days with a 2-day break in-between. However, to minimize missed intervention dates of out-patients e.g. due to sickness or other significant events, we will allow continuation of treatment if the 10 sessions can be realized within three weeks.

